### Sample size calculation

The study used superiority design approach. Due to the lack of clinical studies of methotrexate and tofacitinib in combination with Wangbi granule, we refer to the previous studies of methotrexate in combination with Wangbi granule for the treatment of RA [25]. In order to observe the deep remission effect of the Wangbi granule on RA condition, the final DAS28 score of the intervention group needs to be at least 0.5 points lower than that of the control group, so the cut-off value δ takes − 0.5. We adopted single-sided calculation whereα is 0.025, β is 0.2, and the sample size is 1:1, then the single group sample size of 155 cases is obtained. Considering a shedding rate of 10%, 170 cases are needed in each group, and the final total sample size is 340.According to the plan, as the lead center, China-Japan Friendship Hospital will complete the intake of 90 samples, and the remaining 5 centers will equally distribute the remaining 250 samples.

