### Statistical analysis

All analysis and data visualization will be performed using IBM SPSS (Version 25.0), R (Version 4.1.1).

Baseline data will be displayed using descriptive statistics (eg, means, SD, median, IQR, proportions). We will test the group balance achieved by randomization through appropriate statistical tests (eg, Student’s t tests, Pearson’s χ^2^ tests). Outcomes with a continuous distribution will be compared between groups using the mean (Student’s t test) and Pearson’s χ^2^ test will be used for binary categorical data where categorical variables are expressed as frequencies and percentages and continuous variables are expressed as means and SD.

Preliminary statistical analysis of the primary outcome data will be performed according to the intention-to-treat principle, and the changes in DAS28 will be compared between patients treated with Wangbi granule and Wangbi placebo, and report the rate of deep remission. Further, two-way repeated measures analysis of variance (ANOVA) will be used to examine any interaction effects of the outcome variables between the two groups at the four time points. Mauchly’s sphericity test will be used to examine the spherical assumptions of the repeated measures ANOVA. Bonferroni-corrected post hoc multiple comparisons will be used to examine simple effects between groups at different time points and at different time points for each group.

Sensitivity analysis will be an essential part of the statistical analysis process to complement the interpretation of the results. Depending on the specifics of the data, the full samples will be divided into subgroups based on information about additional drugs (e.g. NSAIDs), co-existing underlying conditions (e.g. hypertension, diabetes), long-term use of other drugs, etc. The calculations will be re-run in each subgroup to verify the validity of the results. When necessary, a per protocol set (PPS) analysis will be part of the sensitivity analysis. If any variable has no more than 20% missing values, the MICE package in R will be used for multiple interpolation to replace it. For the statistical process, *P* < 0.05 is considered statistically significant.

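### Re-running the tests within baseline subgroups is labelled a sensitivity analysis that verifies the result, which subgroup re-runs cannot do; an interaction model should replace it

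*Protocol article*

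**What the plan says.** In the protocol article, the Statistical analysis section introduces sensitivity analysis as a complement to interpreting the results. Under that label it divides the full sample, depending on the data, by additional drugs such as NSAIDs and by "co-existing underlying conditions (e.g. hypertension, diabetes), long-term use of other drugs, etc". It then gives the method and its purpose: "The calculations will be re-run in each subgroup to verify the validity of the results".

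The calculations that the section names are between-arm comparisons ("Outcomes with a continuous distribution will be compared between groups using the mean", by Student's t test), Pearson's chi-square test for binary data, and a repeated measures ANOVA. The only interaction named is by time: the ANOVA is to "examine any interaction effects of the outcome variables between the two groups at the four time points". The section closes with one threshold for the whole statistical process: P < 0.05 "is considered statistically significant".

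The Sample size calculation section sizes the trial on the full sample only. It requires that "the final DAS28 score of the intervention group needs to be at least 0.5 points lower than that of the control group", with one-sided alpha 0.025 and beta 0.2, and a "single group sample size of 155 cases is obtained".

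**The concern.** A sensitivity analysis re-estimates the same quantity, here the treatment effect in all randomised patients, under different assumptions. A subgroup analysis estimates a different quantity in part of the sample. Agreement between strata does not validate the overall result, and disagreement does not undermine it. The question that a subgroup analysis can address is whether the effect differs between strata. Two separate within-stratum tests do not answer that: one significant and one non-significant stratum is the expected pattern when a uniform effect is tested with too few patients.

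At stake is the reading of the trial. A real and uniform effect could be described as unconfirmed in the smaller strata, or a chance contrast could be taken as a differential effect.

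The point covers only factors fixed before randomisation, such as co-existing disease and established long-term drugs. NSAIDs taken during the trial arise after randomisation, and an interaction model would not repair a split on them.

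**Working it through.** **Inputs from the Sample size calculation section:** difference 0.5 DAS28 points, one-sided alpha 0.025, power 80%, 155 per arm. **From the Statistical analysis section:** threshold P < 0.05. Its sidedness is not stated; I take it as two-sided, which equals one-sided 0.025 in the direction of benefit. **Assumptions:** an identical effect in every patient, and subgroup shares f of 10% to 50%, since the article gives no prevalences.

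**The plan's own figure.** No SD is stated, so 155 cannot be reproduced independently. It corresponds to SD = 0.5 / [(1.96 + 0.8416) × √(2/155)] = 1.57. The subgroup results below do not need this SD. They depend only on the 80% power and on f.

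**Subgroup power.** At the planned power the expected overall z is 1.96 + 0.8416 = 2.80. In a subgroup with share f it is 2.80√f, so power = Φ(2.80√f − 1.96). For f = 0.10: 2.80 × 0.316 = 0.886, and Φ(0.886 − 1.96) = Φ(−1.07) = 14%. For f = 0.50: 2.80 × 0.707 = 1.98, and Φ(0.02) = 51%.

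**Both strata significant.** The strata share no patients, so the probability is the product of the powers at f and 1 − f. If both z values exceed 1.96, so does the overall z, because it equals √f·z₁ + √(1−f)·z₂ and the two weights sum to at least 1. Given a significant overall test, the probability is therefore the product divided by 0.80. A simulation of 1,000,000 draws gave the same values.

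| Split | Power, smaller / larger stratum | Both significant | Both, given overall significant |
|---|---|---|---|
| 10/90 | 14% / 76% | 11% | 13% |
| 20/80 | 24% / 71% | 17% | 21% |
| 30/70 | 34% / 65% | 22% | 27% |
| 50/50 | 51% / 51% | 26% | 32% |

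So at least one stratum is non-significant in 74% to 89% of all trials. If all 170 per arm were analysed, both strata would be significant in 12% to 30%.

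**Higher true power.** At 99% overall power the expected z is 1.96 + 2.326 = 4.29. For 50/50, Φ(4.29 × 0.707 − 1.96) = Φ(1.07) = 0.858, and 0.858² = 74%. For 10/90, Φ(−0.60) × Φ(2.11) = 0.273 × 0.982 = 27%. In terms of SD with 155 per arm, both strata are significant in 28% (10/90) to 77% (50/50) of trials at SD 1.0, and in 41% to 95% at SD 0.8.

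**The interaction test.** With a uniform effect it wrongly signals a difference in 5% of trials per factor (simulated 0.050, and about 0.05 also when the overall test is significant). Its power against an interaction as large as the whole 0.5-point effect is about Φ(2.80√[f(1−f)] − 1.96). For 50/50 this is Φ(1.40 − 1.96) = 29%, and for 10/90 it is Φ(0.84 − 1.96) = 13%.

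**The case against.** The strongest reply is that the article gives no rule for what counts as verified. A reader might infer that every stratum must reach P < 0.05, but the text does not say so. The threshold sentence is a general closing line, and comparing the direction and size of estimates fits the wording equally well. This stands: the percentages above describe one reading, and under a comparison of estimates the problem would be milder.

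A reader might also infer that a valid result would usually look unverified. That depends on the planned 80% power and on the splits. Entry is restricted to DAS28 2.6 to 3.2, the outcome SD is not stated, and it may be below 1.57. At SD 0.8 with a 50/50 split both strata would nearly always be significant. This also stands.

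Nor do the documents support the inference that false subgroup claims will be reported. No such claim is planned, and the primary comparison by intention to treat is untouched.

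Finally, interaction tests are often left to the analysis plan, which is not shown. Their absence here does not prove that none exists, and it is not the point. The point is the stated method and purpose: re-running the tests by subgroup, under the heading of sensitivity analysis, as a check of validity. An analysis plan that followed this text would inherit the error, and the error does not depend on the criterion or on the power.

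**Conclusion.** The point holds as a flaw in a stated rule for a supplementary analysis. Subgroup re-runs on baseline factors cannot verify the overall result at any power, and separate within-stratum tests do not test whether the effect differs. The size is conditional. Under the P < 0.05 reading, a uniform effect and 80% power, both strata of one factor are significant in 11% to 26% of trials, or 13% to 32% given a significant overall result, for assumed splits from 10/90 to 50/50. At 99% power the range is 27% to 74%. The primary analysis, its type I error and the sample size are not affected. The change should still be made, because the wording invites misreading in both directions and costs little to correct.

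**What to change.** For factors recorded at baseline, fit one full-sample model with treatment, factor and treatment-by-factor interaction. Report the interaction estimate and the treatment difference in each stratum with 95% confidence intervals, labelled exploratory. Delete the clause that gives verification as the purpose of the subgroup analyses. Keep the term sensitivity analysis for re-estimating the same overall effect under other missing-data or analysis-set assumptions, such as the per-protocol analysis already mentioned.

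The cost is about two sentences of analysis text and no new data. There are two downsides to state openly. The interaction test has low power (about 13% to 29% for an interaction as large as the 0.5-point effect), so a non-significant interaction must not be read as proof of consistency. And no within-subgroup P value can then be quoted as confirmation.

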Participants may decide to withdraw from the trial at any time for any reason of their own choosing. The investigators may also ask the participant to withdraw from the trial for rational reasons. All participants who have completed the informed consent form and are screened and qualified to enter the randomized trial, regardless of when and why they withdrew, will be treated as dislodged cases as long as they do not complete the observation period specified in the protocol.

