### Safety

Medications including methotrexate, tofacitinib, and Wangbi granule are all commonly used for RA and are not expected to cause unacceptable side effects compared to their therapeutic effects. If an adverse reaction is suspected, treatment will be stopped immediately with the permission of the Principal Investigator. During the trial period, investigator will provide participants with free trial drugs. Participants will have access to some free tests and receive a set amount of subsidy.

An adverse event is defined as any adverse medical event that occurs between the time the participant signs the informed consent and the last follow-up visit, whether or not it is causally related to the study drug. Adverse events will be monitored continuously during the treatment period, regardless of whether adverse events are related to the trial drug, the investigators should fill out the record form truthfully and in detail. A serious adverse event, such as a new or previous exacerbation of the patient’s disease during treatment, must be reported within 24 h. Termination of the trial should be considered when additional immunosuppressive drugs or other medications, surgery or other physical therapy associated with the improvement of RA are indeed required. Such a sample will be treated as an off-case. The study team will continue to track the progress of adverse events.

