### Data management

Investigators and participants obtain the required information in person or by telephone, and investigators will consult the hospital’s medical records system to complete additional details. All the data obtained are recorded in the special paper case report form. The information obtained from the last recording will be used as the final data for participants who withdrew. After the CRO collects the paper documents returned by each research center, these data are stored in a special database for unified management. Epidata software will be used to establish the corresponding database, and the data will be entered synchronously by different data managers, using the two-entry method. The CRO will be in charge of data management. The biological sample are stored in the bio-sample bank of China-Japan Friendship Hospital.

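### Multiple imputation is switched off for any variable with more than 20% missing, leaving only last value carried forward for withdrawals and no stated method for other gaps

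*Protocol article*

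**What the plan says.** Four statements in the protocol article bear on missing DAS28 values.

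- Statistical analysis, on imputation: "If any variable has no more than 20% missing values, the MICE package in R will be used for multiple interpolation to replace it". Since MICE is named, interpolation is read here as imputation. No method is given for a variable above 20%.
- Statistical analysis, on the primary comparison: "Preliminary statistical analysis of the primary outcome data will be performed according to the intention-to-treat principle". The per-protocol set is secondary: "When necessary, a per protocol set (PPS) analysis will be part of the sensitivity analysis". The same section also plans a repeated-measures analysis over four time points: "two-way repeated measures analysis of variance (ANOVA) will be used to examine any interaction effects of the outcome variables".
- Data management, on withdrawals: "The information obtained from the last recording will be used as the final data for participants who withdrew". This is last observation carried forward, and it has no ceiling.
- Eligibility criteria and Safety label some participants without giving an analysis rule. Non-completers "will be treated as dislodged cases as long as they do not complete the observation period specified in the protocol". Of those who need additional RA treatment it is said: "Such a sample will be treated as an off-case".

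The planned loss is in Sample size calculation: "Considering a shedding rate of 10%, 170 cases are needed in each group, and the final total sample size is 340".

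**The concern.** Whether multiple imputation is valid depends on why values are missing and on what the imputation model contains. The percentage missing does not settle it. A ceiling therefore drops the method at the point where the choice of method matters most.

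Three features make this rule a poor one.

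- **It depends on the data.** The primary method is known only once the missing values have been counted.
- **It works per variable.** Week 8 of DAS28 could be left incomplete while weeks 4 and 12 are imputed, within the same repeated-measures ANOVA. Week 8 is the telephone visit.
- **What remains above it is weaker.** Withdrawals get their last recording. Participants who stay in but miss a visit or a test get nothing stated, so the t test, chi-square test and ANOVA would by default use whatever is available.

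The rules also overlap below 20%. A participant who withdraws before week 12 is covered both by multiple imputation and by the last-recording rule, and nothing says which takes precedence.

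**Working it through.** **1. The plan's own figures.** Sample size calculation starts from 155 per group and allows for 10% loss. 155 × 1.10 = 170.5 and 155 / 0.90 = 172.2, so the stated 170 per group (340 in total) is reproduced within rounding practice. Planned loss is 0.10 × 340 = 34 participants. The ceiling is 0.20 × 340 = 68, twice that.

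**2. The switch point.** 68/340 = 20.0%, so the variable is imputed. 69/340 = 20.3%, so it is not.

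**3. How often the ceiling is passed.** With X ~ Binomial(340, p) for the number missing week-12 DAS28, P(X ≥ 69) is:

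| True loss p | P(more than 20% missing) |
|---|---|
| 10% (planned) | about 1e-8 |
| 15% | 0.5% |
| 18% | 15% |
| 20% | 47% |
| 22% | 79% |
| 25% | 98% |

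**4. What the remaining methods would estimate.** The document gives no loss model, visit-by-visit effect or SD, so everything in this step is assumed:

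- The effect (control minus Wangbi) is 0.25, 0.40 and 0.50 at weeks 4, 8 and 12. The final 0.50 matches the difference used in Sample size calculation.
- Correlation is autoregressive at 0.6, so weeks 4 and 12 correlate at 0.6² = 0.36.
- Loss occurs after week 4, with log-odds rising by 0.5 or 1.0 per DAS28 point at week 4.
- SD is 0.8, or 1.57. The latter is back-solved from 155 per group: 0.5 × √(155/2) / (1.960 + 0.842) = 1.57.

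*Equal 25% loss.* The selection terms cancel between arms, whatever the SD or slope. Carrying forward gives 0.75 × 0.50 + 0.25 × 0.25 = 0.4375, about 0.44. Completers give 0.50.

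*Unequal loss.* The completer difference is 0.50 + 0.36 × (shift in control − shift in Wangbi). Each shift is the change in that arm's week-4 mean when only those who stay are counted. Numerical integration gives the following, for slopes 0.5 and 1.0 in turn:

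| SD | Loss, control / Wangbi | Completers | Last value carried forward |
|---|---|---|---|
| 0.8 | 30% / 15% | 0.48, 0.47 | 0.48, 0.49 |
| 0.8 | 15% / 30% | 0.52, 0.53 | 0.41, 0.40 |
| 0.8 | 25% / 20% | 0.49, 0.49 | 0.46, 0.46 |
| 1.57 | 30% / 15% | 0.44, 0.41 | 0.52, 0.54 |
| 1.57 | 15% / 30% | 0.56, 0.59 | 0.37, 0.34 |
| 1.57 | 25% / 20% | 0.48, 0.47 | 0.47, 0.48 |

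Against the true 0.50, the smallest completer bias under a two-fold imbalance is 0.0165/0.50 = 3.3% and the largest is 0.0876/0.50 = 17.5%. Under 25%/20% loss it is about 1% to 6%. A regression on the week-4 value, standing in for a missing-at-random analysis, recovered 0.50 within simulation error in every case. That is expected, because loss was made to depend only on week 4.

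**The case against.** The tempting stronger reading is that above 20% the trial falls back to a completer analysis. The document does not say so. The last-recording rule has no ceiling, so withdrawals keep a written method that is not completers. The primary analysis is labelled intention-to-treat, and the per-protocol set is only a conditional sensitivity analysis. The labels for non-completers and for those needing extra treatment do not say that they leave the analysis. This stands. Available-case analysis is only an inference, and only for values missing in participants who did not withdraw.

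The ceiling is also remote. At planned loss it is practically never reached, and it matters only near twice that loss. This stands too, and limits the priority of the point.

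The bias figures rest on an assumed loss model. The larger ones need an SD of 1.57, which the document never states. Entry DAS28 is restricted to 2.6 to 3.2, so the baseline SD cannot exceed 0.3; a much larger week-12 SD is possible but assumed. The figures are therefore illustrations.

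Finally, an article leaves the details of an imputation model to the analysis plan. That is fair for the details. The ceiling is different: it is a rule the article states, and it is badly fixed as stated.

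**Conclusion.** The point holds in a limited form. The protocol makes multiple imputation conditional on no more than 20% missing in each variable. Above that it leaves last value carried forward for withdrawals and nothing stated for other gaps. A reader might infer a completers-only primary analysis, but the text does not support that.

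The chance of crossing the ceiling for week-12 DAS28 is negligible at the planned 10% loss and becomes real from about 18%. When it is crossed, neither remaining approach is dependable. Under the assumptions above, carrying forward understates a growing effect even with equal loss (0.44 against 0.50). Completers are unbiased with equal loss but off by roughly 3% to 17.5%, in either direction, when loss is two-fold unequal and depends on earlier DAS28. These sizes depend on the assumed SD, slope and effect path. The defect in the rule does not depend on them. It is worth correcting, though not urgent at planned loss.

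**What to change.** - Delete the 20% condition in Statistical analysis.
- Name multiple imputation as the single primary method for missing outcome values whatever the missing fraction. Run it by arm, using baseline and all visits of the outcome.
- Reconcile the last-recording sentence in Data management so that it does not replace multiple imputation for participants who withdrew. It can be dropped, or kept as a labelled sensitivity analysis.
- If a primary variable exceeds 20% missing, keep multiple imputation as the main analysis and add a delta-shift (tipping-point) sensitivity analysis.

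The cost is a sentence in each of two sections and a little extra analysis. No visits or participants are added, and the change can be made before unblinding. The downside is heavier reliance on the missing-at-random assumption when loss is high. The tipping-point analysis shows how far that assumption could fail before the conclusion changes.

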### Data management

Investigators and participants obtain the required information in person or by telephone, and investigators will consult the hospital’s medical records system to complete additional details. All the data obtained are recorded in the special paper case report form. The information obtained from the last recording will be used as the final data for participants who withdrew. After the CRO collects the paper documents returned by each research center, these data are stored in a special database for unified management. Epidata software will be used to establish the corresponding database, and the data will be entered synchronously by different data managers, using the two-entry method. The CRO will be in charge of data management. The biological sample are stored in the bio-sample bank of China-Japan Friendship Hospital.

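### Two unreconciled rules, last recording carried forward and multiple imputation, cover the same missing week-12 DAS28 values, and the protocol does not say which feeds the intention-to-treat analysis

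*Protocol article*

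**What the plan says.** Four places in the protocol bear on participants who do not complete.

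- **Data management** gives a last-recording rule: "The information obtained from the last recording will be used as the final data for participants who withdrew". It names no variable, visit or analysis set.
- **Statistical analysis** gives an imputation rule: "If any variable has no more than 20% missing values, the MICE package in R will be used for multiple interpolation to replace it". It makes no exception for withdrawals and gives no rule above 20%. The sentence stands in the paragraph on sensitivity analysis.
- **Statistical analysis** also sets the principle for the primary outcome, which "will be performed according to the intention-to-treat principle". The per-protocol set has a secondary place: "When necessary, a per protocol set (PPS) analysis will be part of the sensitivity analysis".
- **Eligibility criteria** and **Safety** attach labels. Participants who withdraw "will be treated as dislodged cases as long as they do not complete the observation period specified in the protocol". Of those who need additional RA treatment, the Safety section says "Such a sample will be treated as an off-case". Neither section says what the label means for the analysis.

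The Sample size calculation plans for 10% shedding, which is below the 20% ceiling for imputation.

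**The concern.** A participant who withdraws before week 12 has a missing week-12 DAS28. One section replaces it with the last recorded value and another replaces it with multiple imputations. The two rules generally give different estimates and different standard errors, so the intention-to-treat result depends on a choice that the protocol does not make. That choice could still be open once the data are in hand.

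The rules are also not equally good. Carrying a value forward is unbiased only if scores would not have changed after withdrawal, or if the changes would have cancelled between arms. The carried value then enters the t-test and the repeated-measures ANOVA as if it had been measured, which hides the uncertainty. Above 20% missing the imputation rule lapses, and the last-recording rule is the only one left for withdrawals. That is where it can do most harm.

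**Working it through.** **Do the rules overlap?** Planned shedding is 10%, so 170 × 0.10 = 17 participants per arm are expected to be lost and 153 to remain. Since 10% is below 20%, the imputation rule is in force for week-12 DAS28, and the last-recording rule covers the same withdrawals. Both apply.

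**The plan's own figures.** The inputs in the Sample size calculation are a 0.5-point difference, one-sided alpha 0.025, 80% power, 1:1 allocation and 155 per group. No SD is given, so 155 cannot be reproduced. It can only be inverted: SD = 0.5 × √(155/2) / (1.960 + 0.842) = 1.57. For dropout, 155/0.9 = 172.2 and 155 × 1.1 = 170.5. The stated 170 is close to both and is not in dispute here. The SD affects only the power figures below, not the shifts in the estimate.

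**Equal dropout.** I take week 12 as the end point, because treatment ends then. Let q be the dropout in each arm and f the share of the week-12 effect already present at the last recording. Neither the share nor the timing is in the protocol, so a range is shown. The carried-forward estimate is −0.5 × [(1 − q) + q × f]. Approximate power is Φ(|estimate| / (1.57 × √(2/170)) − 1.960), with the SD held at 1.57.

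| q | f | Estimate | Power, n = 170 |
|---|---|---|---|
| 10% | 0 | −0.450 | 75% |
| 10% | 1/3 | −0.467 | 78% |
| 10% | 2/3 | −0.483 | 81% |
| 20% | 0 | −0.400 | 65% |
| 20% | 1/3 | −0.433 | 72% |
| 20% | 2/3 | −0.467 | 78% |

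For comparison, completers alone with an unbiased −0.5 have 79% power (n = 153) and 75% (n = 136).

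**Unequal dropout, no true effect.** Let t be a common trend from the last recording to week 12. The spurious difference is −(q_active − q_placebo) × t.

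- 5% active, 15% placebo, t = −0.3: −(−0.10)(−0.3) = −0.03, in favour of the test drug.
- The same split with t = −0.6: −0.06.
- 15% active, 5% placebo: +0.03 and +0.06, against the test drug.

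**Simulation.** The assumptions are 170 per arm, 1,000 replicates, baseline uniform on 2.6 to 3.2 (the entry range in Table 1), an effect of −0.17 at week 4 and −0.5 at week 12, and dropout after week 4 that is more likely with a higher week-4 score. Mean estimates were:

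| Dropout, active / placebo | Last value | Completers | Regression imputation |
|---|---|---|---|
| 10% / 10% | −0.465 | −0.498 | −0.498 |
| 20% / 20% | −0.434 | −0.501 | −0.501 |
| 15% / 5% | −0.434 | −0.526 | −0.498 |
| 5% / 15% | −0.498 | −0.472 | −0.500 |
| 5% / 15%, no effect, trend −0.3 | −0.035 | +0.030 | +0.001 |
| 15% / 5%, no effect, trend −0.3 | +0.036 | −0.026 | +0.002 |

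Imputation is close to unbiased here by construction, because dropout depends only on a recorded value. The table shows that the choice of rule moves the answer. It does not show that imputation is right whatever the cause of dropout.

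**The case against.** The best defence is that the two sentences can be reconciled. The last recording could serve withdrawals while multiple imputation fills the gaps of those who stay. Alternatively, carrying forward could be the primary approach and imputation the sensitivity analysis, in whose paragraph it stands. Either would be coherent, but the text states neither. A separate analysis plan might choose, but the protocol would still hold two rules for the same values.

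Blinding is a partial safeguard. Under Allocation and blinding, the data are locked first, the analysts then see only groups A and B, and the meaning of the codes follows the analysis. This limits steering towards the test drug. It does not prevent a choice between methods after the size of the difference has been seen.

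The size is also modest. At the planned 10% with equal dropout, the shift is 0.02 to 0.05 points and towards no effect.

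A reader might infer more than the documents support:

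- **That the dislodged and off-case labels are a third rule that excludes participants.** They are status labels. Neither section says that such participants are dropped, imputed or kept, and intention-to-treat is named for the primary outcome. They add ambiguity only.
- **That the last-recording rule leaves nothing to impute.** Missed visits, items and laboratory values of participants who stay would remain.
- **That coding early withdrawals as non-remission is itself a bias.** Entry DAS28 is at least 2.6 and remission is below 2.6, so a carried baseline is always non-remission. Counting withdrawal as non-remission is also a legitimate rule if declared, so this does not count against the method.
- **That a flare before withdrawal would distort the result greatly.** The protocol gives neither a split of dropout between arms nor a flare size, and it does not fix when the last recording is taken relative to withdrawal.

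**Conclusion.** The point holds in this form: two stated rules cover the same missing week-12 DAS28 values at the planned dropout, and the protocol does not say which one governs the primary analysis. The conflict is in the text and is not a detail left to another document.

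The last-recording rule is the weaker of the two. With equal dropout it turns a true 0.5 into about 0.45–0.48 at 10% and 0.40–0.47 at 20%. With a 10-point imbalance and a common trend of 0.3 to 0.6, the bias is about 0.03–0.06 in either direction, so the rule cannot be called conservative. These sizes rest on assumed timing, trend and dropout mechanism. The power figures also rest on the back-calculated SD of 1.57. The case for change rests more on the unresolved choice in the primary analysis than on the size of the bias.

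**What to change.** 1. Delete the last-recording sentence from Data management, or move it to Statistical analysis as a named sensitivity analysis.
2. Name one primary method for missing week-12 DAS28 in all randomised participants: multiple imputation by arm with the MICE package already planned, or a mixed model for repeated measures.
3. Apply that method to DAS28 whatever the missing fraction, so that the 20% ceiling does not leave the primary outcome without a rule.
4. State that dislodged and off-case participants stay in the intention-to-treat set and can be removed only from the per-protocol set.

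The cost is a few sentences and a little programming. The sample size and visit schedule do not change.
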